## Abstract

**Background/Objectives:** Children with Autism Spectrum Disorder (ASD) often display heightened sensitivity to simple auditory stimuli, but have difficulty discriminating and integrating multiple phonological features (segmental: consonants and vowels; suprasegmental: lexical tones) at the syllable level, which negatively impacts their communication. This study aims to investigate the neural basis of segmental, suprasegmental and combinatorial speech processing challenges in Mandarin-speaking children with ASD compared with typically developing (TD) peers. **Methods:** Thirty children with ASD and thirty TD peers will complete a multi-feature oddball paradigm to elicit auditory ERP during passive listening. Stimuli include syllables with single (e.g., vowel only), dual (e.g., vowel + tone), and triple (consonant + vowel + tone) phonological deviations. Neural responses will be analyzed using temporal principal component analysis (t-PCA) to isolate overlapping ERP components (early/late MMN), and representational similarity analysis (RSA) to assess group differences in neural representational structure across feature conditions. **Expected Outcomes:** We adopt a dual-framework approach to hypothesis generation. First, from a theory-driven perspective, we integrate three complementary models, Enhanced Perceptual Functioning (EPF), Weak Central Coherence (WCC), and the Neural Complexity Hypothesis (NCH), to account for auditory processing in ASD. Specifically, we hypothesize that ASD children will show enhanced or intact neural discriminatory responses to isolated segmental deviations (e.g., vowel), but attenuated or delayed responses to suprasegmental (e.g., tone) and multi-feature deviants, with the most severe disruptions occurring in complex, multi-feature conditions. Second, from an empirically grounded, data-driven perspective, we derive our central hypothesis directly from the mismatch negativity (MMN) literature, which suggests reduced MMN amplitudes (with the exception of vowel deviants) and prolonged latencies accompanied by a diminished left-hemisphere advantage across all speech feature types in ASD, with the most pronounced effects in complex, multi-feature conditions. **Significance:** By testing alternative hypotheses and predictions, this exploratory study will clarify the extent to which speech processing differences in ASD reflect cognitive biases (local vs. global, per EPF/WCC/NCH) versus speech-specific neurophysiological disruptions. Findings will advance our understanding of the sensory and integrative mechanisms underlying communication difficulties in ASD, particularly in tonal language contexts, and may inform the development of linguistically tailored interventions.

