However, we acknowledge that this local/global conceptual distinction may not fully reflect the neurophysiological reality or complexity of speech perception and thus may not represent the EPF/WCC models accurately. As mentioned earlier, consonant and vowel perception is not purely based on “local” or “isolated” segmental features in the abstract sense as they may involve integration of multiple acoustic cues (e.g., VOT, formant transitions), which can place significant demands on global processing mechanisms. Given the exploratory nature of this study, we treat this framework as provisional—a hypothesis-generating lens to be validated against empirical data.

In contrast to the theory-driven approach, Table 2 specifies predictions based on empirical findings from the MMN literature, focusing on how each stimulus condition may behave in ASD, regardless of theoretical assumptions. When additional features are involved for more complex processing, presumably the MMN differences in amplitude and latency will be magnified in the tired system going from single- to dual- to triple- feature contrasts due to integration difficulties in ASD reported in the literature. While the overall data-driven hypothesis from the MMN literature is that children with ASD will show reduced MMN amplitudes and prolonged latencies across all speech stimulus conditions with effects worsening with complexity, vowel processing stands as a notable exception. As reviewed earlier, some studies have found that children with ASD exhibit prolonged MMN latencies (but not reduced MMN) for vowel stimuli and reduced P3a responses, indicating delayed sensory encoding and impaired attentional orienting to vowel changes. Especially when considering individual variability in language ability or sensory preferences, intact MMN responses may also occur for various speech contrasts (including consonants and vowels) in some subgroups of ASD populations. It is also worth noting that not all MMN studies explicitly report hemispheric data for MMN analyses. Given the growing body of evidence indicates atypical hemispheric specialization for speech in ASD, we tentatively hypothesize that this reduced left-hemispheric MMN advantage (which is not specified in WCC/EPF/NCH models) will be evident across all stimulus conditions, particularly for complex, linguistically relevant contrasts.

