#### 2.3.3. Temporal Principal Component Analysis

Given the use of a multi-feature oddball paradigm in the present study, the ERP components elicited by different deviant types are likely to overlap temporally, making it challenging to isolate the MMN using conventional fixed-window analysis. Prior studies have successfully applied temporal principal component analysis (t-PCA) to decompose overlapping ERP components and better isolate specific responses such as the MMN in oddball paradigms [73,74]. To address this issue, this study will employ t-PCA, a data-driven approach to decompose the ERP signal into latent temporal components. t-PCA enables the extraction of principal components that account for the majority of variance in the time domain, and through rotation and back-projection, allows psychologically meaningful components to be reconstructed in ERP space [75]. Compared to traditional averaging methods, t-PCA offers improved component separation, higher signal-to-noise ratio, and greater sensitivity in detecting condition-specific effects—advantages particularly critical for paradigms involving multi-dimensional speech feature processing (see Figure 2).

To extract multiple ERP components elicited by the multi-feature oddball paradigm, including early mismatch negativity (eMMN), and late mismatch negativity (lMMN), we decompose the time-domain covariance structure of the ERP data and identifies latent temporal components that account for the greatest proportion of variance in the signal.

t-PCA is applied across all conditions and participants, using the covariance matrix and Promax oblique rotation to enhance interpretability and allow for potential correlations among components. Component selection was guided by three criteria: (1) latency and temporal distribution of the component; (2) polarity and waveform characteristics; and (3) topographic distribution across the scalp. Based on previous literature and the typical temporal-spatial profiles of the target components, the following components are identified:eMMN: Early mismatch negativity (~100–200 ms; Fz, FCz, Cz)lMMN: Late mismatch negativity (~200–300 ms; Fz, FCz, Cz)P3a: Fronto-central positivity (~250–350 ms; Fz, FCz, Cz)

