Once identified, components are back-projected into ERP space by multiplying temporal loadings with corresponding factor scores for each condition and participant. This is achieved by multiplying the component loadings with the corresponding factor scores for each condition and participant and reprojecting the resulting signal onto the original time axis. The reconstructed waveforms retain the component-specific variance structure while being interpretable in microvolt (µV) units, to facilitate traditional ERP analysis. For each reconstructed component (eMMN, lMMN, and P3a), mean amplitudes are calculated over representative electrode sites within the corresponding time windows. These values are then used in statistical analyses to assess condition effects and group differences in auditory feature processing. Importantly, we selected t-PCA because it enhances sensitivity to subtle neural effects by disentangling overlapping ERP components, isolating latent temporal patterns that may be masked in raw waveforms, and reducing noise through variance-based decomposition [76]. This is particularly critical in multi-feature paradigms, where temporal overlap between components (e.g., eMMN, lMMN, P3a) can obscure condition- and group-specific neural differences.

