#### 3.2.2. RSA-Level Predictions

P10 (Weaker Representations): Neural RDMs in the ASD group will show lower overall dissimilarity between deviants and standards across all conditions, with the greatest reduction in C + V + T.

P11 (Atypical Weighting): The fit between neural RDMs and a “Complexity-Weighted” model (which predicts linear degradation with added features) will be stronger in the ASD group than in TD children.

P12 (Hemispheric Asymmetry): Representational dissimilarity in the left hemisphere will be disproportionately reduced in the ASD group, particularly for tone-involving and multi-feature conditions, reflecting a lack of typical left-hemisphere specialization for speech.

The dual-prediction framework allows us to test competing accounts of speech processing in ASD. The predictions are focused on measurable outcomes (overall MMN amplitude, latency, and representational structure) rather than on speculative subcomponents. While we will use t-PCA to decompose the ERP signal and ensure accurate extraction of the MMN, we do not make strong a priori predictions about the distinct roles of early vs. late MMN due to the lack of specific empirical evidence in the ASD literature for multi-feature speech paradigms. Instead, any differences in the temporal dynamics of the MMN will be explored post hoc and reported as exploratory findings, not as confirmatory predictions. By grounding our predictions in established frameworks and focusing on robust, falsifiable outcomes, we ensure a transparent and rigorous evaluation of how Mandarin-speaking children with ASD process and integrate speech features.

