**Figure 3 brainsci-15-00905-f003:**
[figure not shown]
Workflow of RSA applied to ERP data from a multi-feature oddball paradigm.

**Table 1 brainsci-15-00905-t001:** Tentative Predictions for the Seven Stimulus Conditions (Based on EPF/WCC/NCH) Condition.

	Processing Type	Prediction in ASD	EPF + NCH Account	WCC + NCH Account
Consonant only	Local	↑ or = MMN amplitude ↓ or = MMN latency	Enhanced perception of phonetic detail	Intact
Vowel only	Local	↑ or = MMN amplitude ↓ or = MMN latency	Enhanced formant processing	Intact
Tone only	Global	↓ MMN amplitude ↑ MMN latency	Reduced prosodic integration	Impaired due to global integration load
C + V	Mixed/Global	↓ MMN amplitude ↑ MMN latency	Disruption due to multiple feature load	Integration weakness
V + T	Global	↓↓ MMN amplitude ↑↑ MMN latency	Disrupted holistic processing	Poor feature binding
C + T	Global	↓↓ MMN amplitude ↑↑ MMN latency	Disrupted holistic processing	Failure to form unified percept
C + V + T	Global	↓↓↓ MMN amplitude ↑↑↑ MMN latency	Collapsed integration under complexity	Strongest integration failure

Note: ↑ represents significant increase. ↓ represents significant decrease. = represents similar results when comparing MMN responses in ASD group with those in the TD group. Double/Triple arrows indicate magnitude increment/decrement.

**Table 2 brainsci-15-00905-t002:** Specific Predictions Based on MMN Literature-Based Predictions for Each Stimulus Condition.

Condition	MMN Amplitude in ASD	Latency in ASD	Reduced Left-Hemispheric MMN Dominance
Consonant only	↓	↑	Predicted—based on broader speech processing literature
Vowel only	= or ↓	↑	Predicted—but may be less pronounced than for consonants
Tone only	↓	= or ↑	Predicted—particularly for lexical tones
C + V	↓↓	↑↑	Predicted—likely pronounced
V + T	↓↓	↑↑	Predicted—key for tonal languages
C + T	↓↓	↑↑	Predicted—reflects integration challenge
C + V + T	↓↓↓	↑↑↑	Predicted—most pronounced reduction expected

Note: ↑ represents significant increase. ↓ represents significant decrease. = represents similar results when comparing MMN responses in ASD group with those in the TD group. Double/Triple arrows indicate magnitude increment/decrement.

**Table 3 brainsci-15-00905-t003:** Phonological Stimuli: Standard vs. Deviant Feature Variations.

Stimulus Type	Stimulus	Feature(s) Changed
Standard	/ba1/	None
Deviant 1	/ba4/	Tone change
Deviant 2	/bu1/	Vowel change
Deviant 3	/da1/	Consonant change
Deviant 4	/bu4/	Tone + Vowel Change

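### A reduced left-hemisphere MMN advantage is predicted for all seven conditions, but the only electrodes named for the components are midline and no hemisphere contrast is defined

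*Protocol article*

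**What the plan says.** **The prediction.** The Abstract introduces the data-driven framework with "we derive our central hypothesis directly from the mismatch negativity (MMN) literature" and includes in that hypothesis "prolonged latencies accompanied by a diminished left-hemisphere advantage across all speech feature types in ASD". Section 1.4 puts it more cautiously, as a tentative hypothesis, but with the same reach: the reduced left-hemisphere advantage "will be evident across all stimulus conditions, particularly for complex, linguistically relevant contrasts". Table 2 gives it a column, "Reduced Left-Hemispheric MMN Dominance", and every one of the seven deviant rows is marked as predicted. P12 in section 3.2.2 states it for RSA: "Representational dissimilarity in the left hemisphere will be disproportionately reduced in the ASD group". The Discussion presents hemispheric asymmetry as a main element of the analysis.

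**The measures.** Section 2.3.3 lists the components with their windows and sites: "Early mismatch negativity (~100–200 ms; Fz, FCz, Cz" and "Late mismatch negativity (~200–300 ms; Fz, FCz, Cz", with the same three electrodes for P3a. It then says that, for the reconstructed components, "mean amplitudes are calculated over representative electrode sites within the corresponding time windows"; those representative sites are not listed separately. In section 2.3.4, Step 2 takes a mean amplitude per stimulus and time window without naming channels. Step 3 compares matrices by time window and by group. Section 2.3.1 plans a 32-channel recording on the 10–20 system.

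**The concern.** Fz, FCz and Cz all lie on the midline. A smaller MMN there could come from a weaker left-hemisphere response, a weaker right-hemisphere response, or both, and the amplitude does not tell these apart. A reader who applies the article as written would extract values from which no left-right difference can be formed, although such a difference is predicted in every condition.

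Two things are at stake. First, a whole column of Table 2 has no matching outcome. Second, if the channels are chosen only once the data are open, a 32-channel montage offers many possible left-right pairings. A laterality result from a pairing chosen at that stage could not be read as a test of a stated prediction. That matters because the Discussion would treat a confirmed asymmetry as important evidence of atypical neural organisation.

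**Working it through.** The plan states no figure on this point, and no sample-size or power calculation enters. The check sets the prediction against the measures.

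**Step 1: what the prediction needs.** For child i, condition c and component k, the smallest sufficient measure is a laterality contrast

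L(i,c,k) = mean amplitude over a left channel set − mean amplitude over the mirror-image right set.

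A reduced left advantage in ASD is a group difference in L, which is the group × hemisphere interaction.

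**Step 2: what the named sites supply.**

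| Component | Named sites | Left | Right |
|---|---|---|---|
| eMMN | Fz, FCz, Cz | 0 | 0 |
| lMMN | Fz, FCz, Cz | 0 | 0 |
| P3a | Fz, FCz, Cz | 0 | 0 |

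Both terms of L are empty, so L is undefined for every child, condition and component.

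**Step 3: how many predictions are affected.** Table 2 has seven conditions (C, V, T, C+V, V+T, C+T, C+V+T). All seven carry a laterality prediction, so 7 of 7 have no defined measure at component level.

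**Step 4: RSA.** P12 needs dissimilarities computed separately for the left hemisphere and, for the word disproportionately to have meaning, for the right as well. Step 2 forms one neural matrix per time window. The four theoretical models in Step 1 differ only in how tone, vowel and consonant are weighted. Step 3 splits by window and group. None of the three steps contains a hemisphere split.

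**Step 5: other places where a measure might be defined.** Section 1.4 gives the MMN focus as amplitude, latency and temporal coordination. The close of section 3.2.2 gives the measurable outcomes as overall MMN amplitude, latency and representational structure. Laterality is in neither list. Nowhere does the article name a lateral site, a laterality index or a hemisphere factor.

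**The case against.** The strongest reply is that the article leaves the point open and does not exclude it. The midline sites appear as typical profiles used to identify components, after a criterion on scalp topography. Amplitude extraction is described separately, over representative sites that are not named. The Figure 2 caption gives the t-PCA data matrix an electrode dimension. RSA is described as multivariate, and one of its two permitted distances, Pearson correlation, needs a vector of values per stimulus. All this is compatible with multichannel input from which left and right sets could be drawn, and lists of lateral electrodes are often left to a fuller document.

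Much of that stands. A reader might infer that the whole analysis is confined to the midline, or that P12 could never be tested. The documents support neither: RSA is not restricted to those sites, and lateral channels belong to the planned recording.

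It does not remove the point. The article does name electrodes for every component, and those it names cannot serve its own hypothesis. The topographic criterion selects components; it is not an outcome compared between groups. For P12 the quantity is named, but the channel grouping that would produce it is not.

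It is also fair to say that laterality belongs to one of two frameworks, is called tentative in section 1.4, is absent from the four key questions there, and sits in a study described as exploratory. That limits its weight, but a tentative prediction still needs a measure.

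**Conclusion.** The point holds in this form: the component amplitudes, at the only sites the article names, carry no left-right contrast. The laterality column of Table 2 (seven of seven entries) therefore cannot be tested as specified, and P12 has no hemisphere-specific matrix defined for it. This rests on reading the representative sites in section 2.3.3 as the three named there, since the article names no others for these components.

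The damage is bounded. The amplitude and latency parts of the data-driven hypothesis are unaffected. A reader might also infer that laterality is all that separates the data-driven framework from EPF/WCC/NCH, so that the comparison of frameworks fails without it. The tables show otherwise. For consonant-only deviants, Table 1 predicts raised or equal amplitude and shortened or equal latency, while Table 2 predicts reduced amplitude and prolonged latency. Vowel-only latency differs as well. What section 1.4 and the Discussion do say is that EPF/WCC/NCH do not specify the laterality prediction.

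**What to change.** Before laterality is examined, and with the date recorded:

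- **Channels.** Name symmetric left and right sets from the recorded montage, for example F3/C3 against F4/C4. The article gives no channel list, so their presence has to be confirmed first.
- **Component amplitude.** Extract eMMN and lMMN amplitude at both sets, form one laterality contrast per child averaged over the deviants, and compare it between groups as the group × hemisphere test. Treat the individual rows of Table 2 as follow-up.
- **P12.** Compute neural matrices separately from the left and right sets and test group × hemisphere on the dissimilarities themselves, which are what P12 concerns.
- **Midline.** Keep Fz, FCz and Cz for overall amplitude.

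If this is not wanted, take laterality out of the central hypothesis in the Abstract and mark Table 2's column and P12 as having no planned test.

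The cost is wording, with no new participants or recordings. It adds more than one test: two MMN components at two levels of analysis give 2 × 2 = 4 group × hemisphere tests, or 3 × 2 = 6 with P3a. Testing every Table 2 row for both MMN components would add 7 × 2 = 14 contrasts. These belong in the multiplicity family. Section 6 already concedes limited power for interactions, so a null laterality result would be weak evidence of no difference.

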#### 2.3.2. ERP Epoching and Feature Extraction

For each trial, EEG data are segmented into epochs ranging from 100 ms before to 700 ms after stimulus onset. Baseline correction is applied using the pre-stimulus interval (−100 to 0 ms). ERP waveforms are averaged separately for each condition, and the resulting averages are used in subsequent statistical analyses and group comparisons.

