## 3. Predictions Based on Theory- and Data- Driven Perspectives

To guide our analysis and interpretation, we present two complementary sets of predictions derived from distinct sources: (1) a theory-driven framework integrating EPF, WCC, and NCH; and (2) a data-driven framework grounded in the empirical MMN literature. This approach ensures that our expectations are both conceptually motivated and empirically constrained. Predictions are formulated for two levels of analysis: temporal principal component analysis (t-PCA) and representational similarity analysis (RSA). t-PCA will be used to decompose the ERP signal into temporally distinct components (e.g., early MMN, late MMN), from which amplitude and latency estimates are derived. RSA will assess the structure of neural representations across conditions.

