#### 3.1.1. t-PCA-Level Predictions (P)

P1 (Component Variance): The proportion of variance explained by temporally decomposed MMN components (eMMN, lMMN) will be lower in the ASD group for multi-feature deviants (V + T, C + T, C + V + T), reflecting less structured neural responses under high integrative demand.

P2 (Factor Scores): Factor scores for MMN-related components will be significantly reduced in the ASD group, particularly for tone-involving conditions (T, V + T, C + T, C + V + T), consistent with a global integration deficit.

P3 (Temporal Dynamics): The ASD group will show a delayed peak in late MMN (lMMN) components across all conditions, with the greatest delay observed for triple-feature deviants, supporting NCH’s prediction of cascading processing delays.

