#### 3.2.1. t-PCA-Level Predictions

P7 (Amplitude Attenuation): Across all conditions (with the exception of vowel deviation), the ASD group will show lower factor scores for MMN components, with the most severe reductions in multi-feature conditions.

P8 (Latency Prolongation): Peak latencies of eMMN and lMMN components will be systematically delayed in the ASD group, with delays increasing as feature complexity rises.

P9 (Component Blurring): The temporal separation between eMMN and lMMN components will be less distinct in the ASD group, suggesting a breakdown in the normal cascade of auditory processing stages.

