**Figure 2 brainsci-15-00905-f002:**
[figure not shown]
t-PCA pipeline for ERP data in the multi-feature oddball paradigm. (**A**) Data Matrix Setup. The matrix is labeled by Conditions × Time Points × Electrodes, representing trials collected across different stimulus types. (**B**) Covariance Matrix. Covariance matrix is essentially a mathematical tool that helps capture how the data varies over time and across different participants and conditions. (**C**) Principal component analysis. After we obtain the covariance matrix, the next step for t-PCA is to perform eigenvalue decomposition of the covariance matrix to extract the Principal Components from it. These principal components can be seen as new variables extracted from the original EEG signal, which reflect the change pattern of the maximum variance in the data. (**D**) Rotation. The principal components are adjusted using rotation techniques, such as Promax rotation, to improve interpretation. The purpose of the rotation is to make the interpretation between the individual principal components clearer and allow them to have correlations that are more in line with the actual electrical activity of the brain. (**E**) Component identification. By rotating the components, we can begin to identify the individual ERP components that make sense, such as eMMN, lMMN, and P3a. (**F**) Back-Projection and Reconstructed ERP. Components being projected back to ERP space. We multiply the loading matrix of each principal component with the factor scores under each condition to obtain the reconstructed waveform. The reconstructed waveforms contain the specific variation structure of each principal component in the ERP signal, and these waveforms can be interpreted in µV units, like traditional ERP waveforms. (**G**) Amplitude Extraction and Statistical Comparison. This final panel shows mean amplitude extraction from the reconstructed ERP data and reflects statistical testing (e.g., *t*-tests, ANOVA) to assess group differences or condition effects.

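### The pooled temporal PCA gives each component one fixed peak time for all children and conditions, so it cannot supply the latency outcomes of P3, P8 and P9

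*Protocol article*

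**What the plan says.** Section 2.3.3 of the protocol article states that "t-PCA is applied across all conditions and participants, using the covariance matrix and Promax oblique rotation". Each identified component is then rebuilt: "components are back-projected into ERP space by multiplying temporal loadings with corresponding factor scores for each condition and participant". The legend of Figure 2, panel F, repeats the rule: "We multiply the loading matrix of each principal component with the factor scores under each condition to obtain the reconstructed waveform". The only measure that Section 2.3.3 then takes is amplitude: "mean amplitudes are calculated over representative electrode sites within the corresponding time windows".

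Section 3 claims more. It describes the t-PCA components as the source "from which amplitude and latency estimates are derived". Section 5 adds that factor scores allow both the strength and the timing of responses to be compared between conditions and groups.

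Three predictions headed as t-PCA-level rely on timing:
- P3 (Section 3.1.1): "The ASD group will show a delayed peak in late MMN (lMMN) components across all conditions".
- P8 (Section 3.2.1): "Peak latencies of eMMN and lMMN components will be systematically delayed in the ASD group, with delays increasing as feature complexity rises".
- P9 (Section 3.2.1): eMMN and lMMN are less separated in time in the ASD group.

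Key question 2 in Section 1.4 asks whether group differences are cascading delays as opposed to pure amplitude reductions.

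**The concern.** A decomposition pooled over everyone has one temporal loading per component. If only the multiplier on that loading differs between children, the component has no individual latency. P3, P8 and P9 would then be tested on an outcome that cannot vary, and a null result would be guaranteed whatever the children's brains do.

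The amplitude side is also exposed. A response that is delayed but not weakened overlaps the shared loading differently, which changes the score. Table 1 predicts longer latency in five of the seven conditions. Table 2 predicts it in six, with tone unchanged or longer. So the plan itself expects the kind of shift that would disturb its amplitude comparisons, and key question 2 needs the two effects kept apart.

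**Working it through.** **1. Peak time of a reconstructed component.** Inputs: the pooled scope and the reconstruction rule, both from Section 2.3.3. For component k, child i, condition c, electrode e and time t:

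x_k(i,c,e,t) = L_k(t) × s_k(i,c,e)

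Averaging over Fz, FCz and Cz replaces s by its mean and leaves L_k(t) alone. The peak time is the t that maximises |L_k(t)|, and it involves neither i nor c. Therefore:
- P3 and P8: ASD latency minus TD latency = 0 ms, with between-child SD 0 ms. The predicted increase with complexity is also 0 ms.
- P9: the lMMN peak minus the eMMN peak is one number shared by both groups.

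A rule that takes the most negative point could jump between two fixed times when the score changes sign, but that is not a latency measure.

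**2. Why a delay enters the amplitude.** The score is a projection of the child's wave on the loadings, so it depends on the size of the response and on how well its timing matches. A simplified case: a Gaussian response with SD 25 ms (assumed), delayed by 30 ms and projected on the undelayed shape, keeps exp(−30²/(4 × 25²)) = exp(−0.36) = 0.70 of its score, although its true amplitude is unchanged.

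**3. Simulation of the planned pipeline.** From the article: 30 per group, seven deviants, 250 Hz, epochs from −100 to 700 ms, covariance PCA, Promax, and mean amplitude at three fronto-central sites in the 100–200 and 200–300 ms windows. Assumed, because the article gives no values: ten electrodes, six factors, components at 150, 250 and 330 ms with SD 25, 30 and 35 ms, noise, 10 ms between-child jitter, and delays that grow with the number of changed features up to the value shown. True amplitudes are equal in the two groups. The test is a two-sided t-test at 0.05 on the triple-feature deviant, with 100 runs per row.

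| True delay in ASD | eMMN p<0.05 | lMMN p<0.05 | eMMN, TD → ASD (µV) | lMMN, TD → ASD (µV) |
|---|---|---|---|---|
| None | 3% | 6% | −1.46 → −1.46 | −0.52 → −0.53 |
| 30 ms, all components | 80% | 64% | −1.41 → −1.01 | −0.58 → −0.71 |
| 40 ms, lMMN and P3a only | 42% | 93% | −1.45 → −1.40 | −0.77 → −0.48 |

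Each component had exactly one distinct peak latency in every run of every row. In row 2 the eMMN falls to 1.01/1.41 = 72% of TD, while the lMMN looks larger in ASD (0.71/0.58 = 1.22), because the delayed early response leaks into the late factor.

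**4. Sensitivity to the assumptions.** Another set of assumed waveforms (40 datasets per delay) gave a false eMMN difference in 95% of runs at 40 ms. Four further settings (component SD 25–40 ms, jitter 10–25 ms, 30 runs each) gave 33–83% for eMMN at 40 ms and 7–20% at 10 ms.

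**5. Is latency recoverable from the same recordings?** Yes, with care. In the simulation of step 3, peak-picking on the unreconstructed averages (180–320 ms window) estimated a 40 ms lMMN delay as +27 ms, with p<0.05 in 67% of runs against 6% under no delay. When early and late peaks were both delayed by 30 ms, the same rule gave −21 ms, because it caught the delayed early peak. Leaving the PCA makes latency estimable, but the rule still has to be chosen well.

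**The case against.** The article offers some cover. Section 2.3.2 says that "ERP waveforms are averaged separately for each condition, and the resulting averages are used in subsequent statistical analyses and group comparisons", which leaves latency on raw averages open. The closing paragraph of Section 3.2.2 lists overall MMN latency as an outcome and makes differences in temporal dynamics exploratory. Section 6 mentions difficulty in matching components across participants, which sits oddly with one shared decomposition. None of this removes the problem. No passage assigns latency to another measure, Section 3 names the t-PCA components as its source, and an exploratory outcome must still be able to vary.

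Other parts of the objection do stand, and they rule out stronger readings that a reader might infer:
- *Delay is untestable in this study.* No. The limit applies to the stated route. Unreconstructed waves, sums of several components, or group-wise decompositions can all carry latency.
- *P1 also needs separate decompositions.* No. The share of a group's variance carried by a shared factor can be computed from that group's scores and total variance.
- *Using condition averages contaminates the MMN contrast.* Not by itself. Scoring is linear, so the deviant score minus the standard score equals the score of the difference wave. Section 2.3.2 does not exclude subtraction, and an article may leave that step to the full plan.
- *Every amplitude entry in Tables 1 and 2 is biased towards attenuation.* Not shown. Size and direction depend on the waveforms.
- *The confound is peculiar to t-PCA.* No. In the four further settings, plain fixed-window means on raw averages also rejected under a pure 40 ms delay (eMMN 33–87%, lMMN 17–77% of runs).

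**Conclusion.** The point holds for the route that the article states. Sections 3 and 5 are wrong that latency or timing comes from the pooled components or their scores. P3, P8 and the peak separation in P9 have zero variance by that route. This is algebra and needs no assumption beyond one pooled decomposition and component-by-component reconstruction.

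That a true delay can appear as an amplitude difference in P2 and P7 also holds, but its size is only illustrative. Under the assumed waveforms, a pure 30–40 ms delay produced false differences in roughly 30–95% of runs, sometimes as a larger lMMN in ASD. The article gives no component widths, noise level or expected delay, so no single rate can be attached to this study. Key question 2 cannot be answered by the analysis as written, but it can be addressed from the same recordings.

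**What to change.** 1. In Sections 3 and 5, remove latency and timing from what the pooled t-PCA and its factor scores deliver. Keep the pooled t-PCA for amplitude.
2. For P3 and P8, measure latency on unreconstructed deviant-minus-standard waves, with a rule stated before group latencies are examined. One suitable choice is 50% fractional-area latency with jackknife standard errors by group and condition. Simple peak-picking in a fixed window is a poor choice, given the bias in step 5 of the working.
3. Define P9 on those same waves, or by t-PCA run separately in each group with a stated factor-matching criterion. P1 can stay on the shared loadings.
4. Report each amplitude difference beside the corresponding latency difference and its confidence interval. A non-significant latency shift must not be read as proof of no delay, so attenuation should be claimed only as far as that interval allows.

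The cost is changed wording and one extra latency analysis, with no new data. Jackknife latencies are group-level statistics, and the group-wise option for P9 adds a factor-matching step.
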